#### Text messages

3.5.1

After the in-person sessions, all participants will receive text messages for the duration of the study (approximately 4 text messages per week) that reinforce information discussed. The messages are the same for each participant (based on group assignment), sent in the same order, and participants are asked to reply back “1” after reading. The messages are framed by the Information-Motivation-Behavioral Skills Model, specifically providing information, addressing factors that influence motivation, and reinforcing skills [34]. Approximately every 1-2 weeks, study staff will verify with each participant that they are receiving text messages.

### Research staff training & fidelity

3.6

Training will be provided for research team members and refreshed every 3 months. The in-person sessions are scripted to enhance fidelity. The PI will routinely observe research staff conducting sessions for fidelity.

### Retention

3.7

To promote retention, we will schedule meetings with participants at times convenient for them, including while receiving hemodialysis. Participants receive incentives for completing the baseline and end of study visits, as well as a fitness watch (e.g., Garmin) at end of study (intervention participants will keep the one they received during the intervention; attention control participants will receive a new fitness watch), and if they participate in an optional 1:1 interview (intervention participants only).

### Study endpoints

3.8

Data will be collected at baseline, week 6, and end of study (week 12). Baseline and end of study assessments will be done in-person. The week 6 assessment will be either by phone or in person.

#### Primary endpoint

3.8.1

The primary study endpoints are feasibility and acceptability. We will examine recruitment, enrollment, and attrition metrics. We will measure adherence to the intervention, defined as participating in at least two progressive muscle relaxation sessions per week, which will be evaluated via individual login accesses and duration of each access to the study website, and having at least two days per week where they met their step goal, evaluated via the fitness watch. We will evaluate adherence to the text messages by evaluating number of messages read compared to the number of messages sent. We will also evaluate acceptability via Likert scale, visual analogue scale, and open-ended questions. Additionally, intervention participants will have the option to participate in an optional 1:1 interview to further explore acceptability of the intervention at the end of the study.

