### Formative work results

2.1

The patient partnership board (n = 3) was comprised of two females and one male, mean age was 65.3 years (range 30-84), and duration of hemodialysis ranged from 2.5 to 7.5 years.

The board described their fatigue, and three themes (Appendix B) emerged from analysis: (1) fatigue is a multifaceted, mind-body symptom (it was both constant and intermittent (having “good and bad days”), it made you not want to do things, and it had a mental and emotional component), (2) there were few things that made fatigue better (moving around, attitude, and time since the last hemodialysis treatment potentially made fatigue better), and (3) receiving hemodialysis and one's health status made fatigue worse (hemodialysis led to fatigue, as did comorbid health conditions and physical inactivity).

After presenting the two interventions, the board was asked what may hinder or promote engagement with the intervention. Three themes (**Appendix C**) emerged for what may hinder engagement: (1) the participants' attitude, mindset, and mood, (2) the participants’ health status (“good and bad days”, symptoms), and (3) progressive muscle relaxation will require practice. Conversely, when asked about what may promote engagement, six themes (**Appendix C**) emerged: (1) doing both progressive muscle relaxation and increasing steps seemed reasonable, (2) individualized, tailored plan for step goals, (3) individualized plan of when participants would do progressive muscle relaxation, (4) interesting in-person training and make it fun to do, (5) positive feedback and encouragement, and (6) adherence monitoring via technology and self-tracking.

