### Study setting & recruitment

3.2

Participants will be recruited from UIC, UI Health, and select dialysis facilities with which the study team has relationships. The study team will review electronic medical records to identify those who meet inclusion criteria identifiable via chart review: age ≥18 years, diagnosis of ESKD and receiving hemodialysis for >3 months, and being able to read and speak English; and have none of the chart-identified exclusion criteria: unstable angina, unstable pulmonary disease or pulmonary symptoms that preclude participation, lower-extremity amputation (below or above the knee amputation) without prosthetic, orthopedic or neurologic condition that would preclude walking or tensing/releasing of muscles, cognitive impairment that precludes trial participation, or any other condition that would preclude participation as deemed by the researchers. We will not include patient partnership board members or patients deemed unable to participate, as determined by their nephrologist. Framed by the recommendations of the board, we will recruit participants by approaching them at the dialysis clinic. If they express interest in learning more about the study, a study staff member will provide them with an informational handout and tell them about the study. Additionally, there will be flyers in the waiting room. A passive mailing or emailing strategy may also be used for recruitment at UI Health.

Interested individuals will be screened in person at the dialysis clinic or over the phone, per the individual's preference, to ensure the individual meets inclusion/exclusion criteria after they provide verbal consent to undergo screening. Screening will consist of clarifying any inclusion or exclusion criteria that were not clear on chart review and asking whether they meet the self-reported inclusion criteria, specifically having a fatigue score ≥4 over the last week measured via visual analogue scale (0 being no fatigue and 10 being extreme fatigue), being able to stand and walk one block, and having a cell phone that can receive text messages. Individuals meeting eligibility will be offered the opportunity to complete the consent process and be enrolled.

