### Interventions

3.5

***Fight Fatigue*-** The *Fight Fatigue* intervention was informed by two evidence-based interventions (progressive muscle relaxation [31,32] and an increased step count intervention [33]), through our work with a patient partnership board, and guided by the Information-Motivation-Behavioral Skills Model [34]. We combined and refined these interventions to meet the needs and preferences of adults with ESKD, as described above. Refinements suggested by the board were integrated if they aligned with the goal of the intervention (reduce fatigue), maintained the fidelity of the evidence-based interventions, aligned with the guiding theory (Information-Motivation-Behavioral Skills Model), and did not increase participant risk. The intervention delivery is framed by the Information-Motivation-Behavioral Skills Model to support behavior change by providing information to support knowledge, identifying and addressing factors that influence motivation, and assuring that participants have the necessary skills to perform the intervention activities [34].

The *Fight Fatigue* intervention is delivered via two, scripted in-person education/training sessions followed by text messages. During the in-person sessions, participants will learn and practice progressive muscle relaxation and how to increase steps, as well as be provided with written instructions and a place for tracking progressive muscle relaxation times and reaching one's step goal. Progressive muscle relaxation training will begin with a description of the rationale for progressive muscle relaxation, followed by training and demonstration of the tension/relaxation 16-muscle sequence [31,32]. After learning the 16-muscle sequence, the 7- and 4-muscle sequences will be taught [31,32]. Participants will be instructed not to tense/relax muscle groups that are injured or cause pain. After the first training session, participants will be instructed to practice progressive muscle relaxation for 20 min at least 2 days/week. Each participant will receive a unique login to a study-specific website that contains recordings of the progressive muscle relaxation 16-, 7-, and 4-muscle sequences. Progressive muscle relaxation recordings have been used in other studies integrating home-based progressive muscle relaxation [35].

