### Data analysis

3.9

The study hypothesis is that the recruitment ratio (percent of approached individuals who agree to participate) will be >60%, retention (percent of randomized individuals who complete the final 12-week study assessment) will be >80%, and adherence among retained participants (at least two progressive muscle relaxation sessions/step goal achieved per week; text messages read) will be >70%. We hypothesize that greater than 80% of retained participants will rate the study as acceptable (rating of agree or higher on end of study acceptability questions). Feasibility metrics and baseline descriptive statistics will be summarized. We will evaluate acceptability via Likert-scale, visual analogue scale, and open-ended questions. Mean scores will be calculated, and scores in the range from disagree to strongly disagree will be considered unacceptable conditions. Open-ended question answers will be summarized by the PI, and the summary will be reviewed by a research team member to verify accuracy. Adherence will be evaluated via fitness watch (steps) and number/duration of accesses on the website. Additionally, steps will be evaluated via accelerometer. Text message adherence will be assessed based on messages sent and read.

We will then estimate within group variability of change in the secondary outcome measure (FACIT-Fatigue) to appropriately power the future, fully powered trial informed by this feasibility trial. We will estimate correlation structure between the secondary outcome measure and Kt/V, dialysis fluid removal, dialysis dose, blood pressure and heart rate, change in blood pressure during treatment, number of missed dialysis treatments, medications, body mass index, weight, hemoglobin, albumin, and phosphorus to appropriately assess power for the future, full powered trial.

For missing data, we will use a complete case approach, as our preliminary work suggests low rates (<1%) of missing data. Multiple imputation methods will be used as sensitivity analyses to ensure robustness of findings if there is higher missingness than anticipated. We will monitor missing data and identify predictors of missingness, specifically evaluating demographic factors, including but not limited to age and sex, as predictors of missingness, and examine the acceptability of outcome measures to inform the future efficacy trial.

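### Website log-ins are the only named source for relaxation-practice adherence, so practice done without the site is not captured and a missed >70% criterion cannot be separated from low website use

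*Protocol article*

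**What the plan says.** The Primary endpoint section (3.8.1) sets the PMR part of intervention adherence, "defined as participating in at least two progressive muscle relaxation sessions per week", and gives its data source: "which will be evaluated via individual login accesses and duration of each access to the study website". The Data analysis section (3.9) repeats it: "Adherence will be evaluated via fitness watch (steps) and number/duration of accesses on the website". Neither section names another source for PMR. Section 3.9 sets the target at more than 70% among retained participants.

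The Interventions section (3.5) describes how PMR is delivered:
- "During the in-person sessions, participants will learn and practice progressive muscle relaxation and how to increase steps".
- Participants are "provided with written instructions and a place for tracking progressive muscle relaxation times and reaching one's step goal".
- They are told to practise for 20 minutes on at least two days a week. This instruction does not mention the website.
- Each participant gets a personal login to a site holding recordings of the three muscle sequences.

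Under Study setting & recruitment (3.2), the only technology criterion is "having a cell phone that can receive text messages".

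**The concern.** The endpoint is meant to measure whether people do PMR, but the instrument measures whether they open a website. The two agree only if home practice always runs through the site, and the article does not require that. A participant can follow every printed instruction, practise from the written sheet or from memory, note the times in the record provided, and leave no trace in the one source used for the endpoint. A participant whose phone takes texts but who has no ready web access meets the stated entry criteria and could be in the same position.

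PMR is one of the two behaviours that define intervention adherence in a primary feasibility endpoint, and it carries a numerical target. If the target is missed, the team needs to know whether patients were unwilling to practise or simply did not use the site. Those answers lead to different designs for the next trial, and log-in data alone cannot tell them apart.

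**Working it through.** **Inputs from the article**
- 40 participants (Sample size), randomized 1:1 (Randomization): 40/2 = 20 in the intervention arm.
- Attrition of at most 20% (Sample size): 20 × 0.80 = 16 retained.
- Target: above 70% among those retained (Data analysis).

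**Inputs that are assumptions**, because the article gives neither
- *a*: the true share of retained participants who do at least two sessions a week.
- *f*: the share of those adherent participants who practise off-site, so that the website does not show two sessions a week for them.
- The 70% is read as a share of participants. The article does not say whether it refers to participants, weeks or sessions.

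**The plan's own figure.** The article prints no figure for off-site practice. It does state a 14% maximum error for retention and completion rates. Assuming a 95% level, 1.96 × √(0.70 × 0.30/40) = 14.2%, and with 32 retained, 1.96 × √(0.80 × 0.20/32) = 13.9%. Both round to 14%, and the figure is not disputed here. PMR adherence, however, is measured in the intervention arm only: with 16 people, 1.96 × √(0.70 × 0.30/16) = 22.5 points. The under-count below comes on top of that sampling error.

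**Step 1. Whole participants.** Suppose all 16 adhere. If 4 are off-site, 12/16 = 75% and the target is met. If 5 are off-site, 11/16 = 68.8% and it is missed. With all 20 retained, 6 off-site gives 14/20 = 70.0%, which is not above 70%.

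**Step 2. Break-even share.** Measured adherence = *a*(1 − *f*). It reaches 70% at *f* = 1 − 0.70/*a*:

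| True adherence *a* | Off-site share at which the measured rate is 70% |
|---|---|
| 75% | 6.7% |
| 80% | 12.5% |
| 85% | 17.6% |
| 90% | 22.2% |
| 100% | 30.0% |

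**Step 3. Chance of meeting the target.** With 16 retained, at least 12 must be counted adherent. The exact binomial probability of 12 or more out of 16, with success probability *a*(1 − *f*), is:

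| *a* | *f* = 0 | *f* = 10% | *f* = 20% | *f* = 30% |
|---|---|---|---|---|
| 80% | 0.798 | 0.521 | 0.261 | 0.098 |
| 85% | 0.921 | 0.684 | 0.382 | 0.157 |
| 90% | 0.983 | 0.827 | 0.521 | 0.235 |

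**Units.** *f* is a share of adherent participants, not of practice sessions. Someone who does three sessions a week, one of them off-site, still shows two on the site and still counts. If instead everyone does exactly two and each is off-site independently with probability 17.6%, only 0.824² = 68% of weeks keep both. The break-even values therefore cannot be read as percentages of practice.

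**The case against.** **Log-ins are objective and self-report tends to inflate.** This stands. A measure that errs towards under-counting is a defensible choice for a feasibility target, and letting a self-completed sheet alone decide the target would trade one bias for another. It argues for keeping the website figure, not for leaving it as the only one.

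**Participants may do nearly all home practice with the recordings.** This is possible. The article supplies recordings of all three sequences and notes that other home-based PMR studies used them. A reader might infer that participants are taught to practise without the site, but the article does not say so. It only leaves practice untied to the site, so the size of the under-count is unknown.

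**Other inferences go further than the text.**
- That off-site practice is scored as non-adherence by rule: no scoring rule is printed. It follows only that such practice is invisible to the named source.
- That someone without web access can never be adherent: this assumes that such people enrol and get no help. The researchers may also exclude people for conditions that preclude participation.
- That log-ins fade as people master the technique: nothing in the article supports this.
- That the plan goes against its patient board: "adherence monitoring via technology and self-tracking" appears in Formative work results as a theme about what promotes engagement, not about how to measure the endpoint. Giving participants a tracking record already answers it.
- That an open page counts as practice: access duration is recorded and guards against this in part.

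**Interviews and open-ended questions could reveal off-site practice.** They could show that it happens. The interviews are optional, and neither source would give a weekly session count to set against the target.

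**Conclusion.** The point holds in this form: the article names website access, twice and with no alternative, as the source for PMR adherence, while its own intervention lets participants practise without the site and hands them a record that the endpoint does not use. Log-in adherence is therefore likely to under-count whatever practice takes place off-site.

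The size cannot be fixed from the article. Under the stated assumptions, modest off-site shares are enough to change the result against the target: about 18% of adherent participants at 85% true adherence, or 5 of 16 when everyone adheres. At 80% true adherence and 16 retained, a 20% off-site share cuts the chance of meeting the target from 0.80 to 0.26. If almost everyone uses the recordings, the effect is negligible. The documents do not support saying that the target will be missed, or that log-ins are an invalid measure. They support saying that a miss could not be interpreted. The change is worth making before follow-up starts, because practice not recorded at the time is hard to recover later.

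**What to change.** Collect the tracking record that participants already receive, described as "a place for tracking progressive muscle relaxation times", and report PMR adherence in two ways:
1. **Website-verified sessions**, from log-ins and access duration. This is objective but does not see off-site practice, and the log-in-only figure should carry this label rather than stand for PMR adherence as a whole.
2. **Website-or-self-recorded sessions**, counting a session found in either source. This sees off-site practice but may be inflated by self-report.

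Read the >70% criterion against both. If both pass or both fail, the conclusion does not depend on the source. If only the second passes, the finding is low website use or over-reporting, and the next trial can be planned with that in view.

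The cost is some data entry and possible self-report over-statement, which showing the two figures together makes visible. The end-of-study visit is in person and gives a sure collection point. The staff contacts every one to two weeks (watch syncing and text-message checks) might also serve, but the article does not say that they are in person, so this needs confirming.

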#### Secondary and exploratory endpoints

3.8.2

The secondary endpoint is fatigue, quantified by the FACIT-Fatigue survey, which assesses 7-day fatigue and is a recommended measure for adults with ESKD [4,38]. FACIT-Fatigue will be evaluated at baseline, week 6, and end of study. Fatiguability will be evaluated with the Pittsburgh Fatiguability Scale, a survey of expected physical and mental tiredness related to various activities [39]. Self-reported sleep quality will be measured with the PROMIS Sleep questionnaire [40]. Pain will be assessed using the PROMIS Pain Intensity and Interference questionnaires [41]. The SF-36 will be used to evaluate self-reported quality of life [42]. Self-efficacy for physical activity will be evaluated using a scale assessing readiness for change to increase physical activity [43]. Given the influence of patient activation on behavior [44,45], the Patient Activation Measure (PAM-13) will be evaluated [46,47]. Since the board described fatigue as a mind-body symptom, we will examine the Whole Person Health Index (WPHI), a self-assessed holistic view of one's health [48].

In addition to questionnaires, we will evaluate daily physical activity and inactivity (e.g., METs, steps, sedentary time, sleep, etc.) as well as sleep quality via accelerometer at baseline and end of study with 1 week wear of the ActiGraph (GT3X), a validated measure of activity and sleep quality that has been used with adults with ESKD [[49], [50], [51]]. Participants will fill out a log while wearing the ActiGraph to report sleep and non-wear times. A minimum of 5 valid days of wear will be included, and a valid day will be considered at least 8 h of wear time, which has been established as an acceptable parameter for reliability [52]. The sampling rate of the devices will be 30 Hz (Hz). For analysis, epoch length will be set to 10 s. Bout parameters and METs will be evaluated using the Freedson (1998) and Freedson EE algorithms [53]. As per other work using the ActiGraph in adults with ESKD, the cut points for analysis will be defined as < 100 counts/min for sedentary time, 100 to 1951 counts/min for light physical activity, and ≥1952 counts/min for moderate-to-vigorous physical activity (MVPA) [54].

At baseline and end of study, we will evaluate parameters collected as part of routine clinical dialysis care, specifically Kt/V (dialysis clearance), body mass index, dialysis fluid removal, number of missed dialysis treatments, blood pressure, heart rate, dry weight, hemoglobin level, albumin level, phosphorus level, and medications.

### Data analysis

3.9

The study hypothesis is that the recruitment ratio (percent of approached individuals who agree to participate) will be >60%, retention (percent of randomized individuals who complete the final 12-week study assessment) will be >80%, and adherence among retained participants (at least two progressive muscle relaxation sessions/step goal achieved per week; text messages read) will be >70%. We hypothesize that greater than 80% of retained participants will rate the study as acceptable (rating of agree or higher on end of study acceptability questions). Feasibility metrics and baseline descriptive statistics will be summarized. We will evaluate acceptability via Likert-scale, visual analogue scale, and open-ended questions. Mean scores will be calculated, and scores in the range from disagree to strongly disagree will be considered unacceptable conditions. Open-ended question answers will be summarized by the PI, and the summary will be reviewed by a research team member to verify accuracy. Adherence will be evaluated via fitness watch (steps) and number/duration of accesses on the website. Additionally, steps will be evaluated via accelerometer. Text message adherence will be assessed based on messages sent and read.

We will then estimate within group variability of change in the secondary outcome measure (FACIT-Fatigue) to appropriately power the future, fully powered trial informed by this feasibility trial. We will estimate correlation structure between the secondary outcome measure and Kt/V, dialysis fluid removal, dialysis dose, blood pressure and heart rate, change in blood pressure during treatment, number of missed dialysis treatments, medications, body mass index, weight, hemoglobin, albumin, and phosphorus to appropriately assess power for the future, full powered trial.

For missing data, we will use a complete case approach, as our preliminary work suggests low rates (<1%) of missing data. Multiple imputation methods will be used as sensitivity analyses to ensure robustness of findings if there is higher missingness than anticipated. We will monitor missing data and identify predictors of missingness, specifically evaluating demographic factors, including but not limited to age and sex, as predictors of missingness, and examine the acceptability of outcome measures to inform the future efficacy trial.

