### Study design & aims

3.1

The study is a 12-week pilot feasibility randomized controlled trial. The study aim is to investigate the feasibility and acceptability of the *Fight Fatigue* progressive muscle relaxation and walking intervention in adults with ESKD and fatigue receiving maintenance in-center hemodialysis (n = 40). The trial is registered at clinicaltrials.gov (NCT07014111) and approved by the University of Illinois Chicago (UIC) IRB (protocol #2025-0281).

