#### Sample size

3.9.1

The sample size will consist of 40 participants, and we anticipate an attrition rate of no greater than 20% based on our team's previous work. This sample size will allow us to assess both feasibility and acceptability to a reasonable level of precision (estimating retention and intervention completion rates within a maximum range of error of 14%), achieve the necessary estimates to design a future, well-powered interventional trial, and it falls within well accepted guidelines on sample sizes for pilot studies of this type [55,56]. We will conduct Intention to Treat and Per Protocol Analyses [57].

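### The 80% acceptability target names no arm, so attention-control participants count towards a criterion meant to judge Fight Fatigue

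*Protocol article*

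**What the plan says.** Acceptability is part of the primary outcome. Under Primary endpoint: "The primary study endpoints are feasibility and acceptability". Study design & aims says what is to be judged, namely whether Fight Fatigue is feasible and acceptable, and describes it as a "progressive muscle relaxation and walking intervention in adults with ESKD and fatigue receiving maintenance in-center hemodialysis".

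Data analysis then makes two statements about acceptability:

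- A target, worded as a hypothesis: "greater than 80% of retained participants will rate the study as acceptable (rating of agree or higher on end of study acceptability questions". The object rated is the study, and the denominator is retained participants.
- A flag, a few sentences later, tied to the mean ratings: "scores in the range from disagree to strongly disagree will be considered unacceptable conditions".

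The same section fixes who is retained by defining "retention (percent of randomized individuals who complete the final 12-week study assessment) will be >80" percent. That definition covers both arms. The only acceptability source limited to the intervention arm is the optional end-of-study interview, which has no threshold.

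**The concern.** The criterion and the aim do not refer to the same people. Control participants receive two sessions and text messages on reading nutrition labels. Their agreement says whether the trial was tolerable to take part in, but nothing about progressive muscle relaxation or step goals. With 1:1 allocation they are about half of the denominator, so high control ratings can lift the pooled figure over 80% when the intervention arm is below it.

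The results are meant to inform a later randomized trial. A pooled pass could be carried forward as evidence that Fight Fatigue met its acceptability target when its own recipients did not reach it.

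The relation between the target and the mean-score flag is a smaller matter. The text does not say which of them governs, or whether the means are taken per arm.

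**Working it through.** **Inputs.** From Sample size: "The sample size will consist of 40 participants", with attrition expected to be at most 20%. From Randomization: 1:1 allocation, so about 20 per arm. From Data analysis: the target is strictly more than 80%. Assumptions: attrition is equal by arm unless stated (16 + 16 = 32 retained), and the Likert scale has five points with agree = 4. The article does not give the scale length.

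**1. The plan's own precision figure.** Sample size quotes a largest error of 14% for retention and intervention completion. The 95% half-width is 1.96 × √(p(1−p)/n).
- p = 0.80, n = 32: 1.96 × √(0.16/32) = 13.9%.
- p = 0.70, n = 40: 1.96 × √(0.21/40) = 14.2%.

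Both round to 14%. The article does not give the p, n or confidence level it used, so the match fits a pooled sample but does not prove one.

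**2. What the pooled target lets through.** Suppose every control participant agrees.

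| Retained (intervention + control) | Agreements needed, pooled | Intervention agreements that suffice | Needed if the intervention arm is judged alone |
|---|---|---|---|
| 16 + 16 = 32 | 26 (81.3%) | 26 − 16 = 10/16 = 62.5% | 13/16 = 81.3% |
| 20 + 20 = 40 | 33 (82.5%) | 33 − 20 = 13/20 = 65% | 17/20 = 85% |
| 13 + 20 = 33 | 27 (81.8%) | 27 − 20 = 7/13 = 54% | 11/13 = 84.6% |

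**3. How often this could happen.** Take independent binomial counts in each arm. Sum the probability of all outcomes in which the pooled count reaches its requirement and the intervention count falls short of its own. With assumed true agreement of 70% (intervention) and 95% (control):
- 16 per arm: pooled pass 0.68; intervention arm alone passes 0.25; pooled pass with arm miss 0.44.
- 20 per arm: 0.60, 0.11 and 0.49.

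Over assumed rates of 60–75% (intervention) and 90–95% (control), the probability of a pooled pass with an arm miss runs from 0.15 to 0.54. These rates are illustrations; the article gives none.

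**4. Target against flag.** If the pooled target is met, the lowest possible mean has every agreeing participant at 4 and everyone else at 1.
- 26/32: (4 × 26 + 1 × 6)/32 = 3.44.
- 33/40: (4 × 33 + 1 × 7)/40 = 3.48.

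Both are above the disagree range, so meeting the target always means escaping the flag. The reverse does not hold: 60% agree and 40% neutral gives 0.6 × 4 + 0.4 × 3 = 3.6, which misses the target without triggering the flag.

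**5. Floor for the intervention arm.** When the pooled target is met with equal retention, the lowest possible intervention mean is (4 × 10 + 6)/16 = 2.88, or (4 × 13 + 7)/20 = 2.95.

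**6. Precision for one arm.** At p = 0.80 the half-width is 1.96 × √(0.16/16) = 19.6 points, or 1.96 × √(0.16/20) = 17.5 points, against 13.9 for 32 pooled.

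**The case against.** The strongest reply is that pooling is inferred. The preceding sentence of Data analysis also speaks of retained participants, for adherence to relaxation sessions and step goals, which only the intervention arm receives. The phrase is therefore not a sure sign of a two-arm denominator. Elsewhere the article calls an arm a condition, so the mean-score flag may already be meant per arm. Tabulation by arm is also something a condensed article often leaves to the full protocol or analysis plan. This lowers certainty about the intent. It does not repair the wording: the target names no arm, it rates the study, and retention is defined over everyone randomized. If the intervention arm was meant, the text needs the same correction.

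Three stronger readings are tempting, and the article supports none of them.

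- **That the target and the flag contradict each other.** They are nested (step 4). The text never says that escaping the flag counts as acceptable. There is a middle zone and an unstated hierarchy, but no contradiction.
- **That Fight Fatigue could be unacceptable to its own arm and still pass.** With equal retention, at least 62.5–65% of the arm must agree, and its mean stays near 2.9 or higher, outside the range that the article calls unacceptable. What is shown is an arm below 80%.
- **That pooled retention is an error.** It is explicitly defined, and overall retention is a legitimate measure for a pilot randomized trial. Showing it by arm as well is useful, but no mistake is being corrected.

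**Conclusion.** The point holds in a limited form. As worded, the primary acceptability target covers both arms, while the aim concerns the intervention. The target can be met at 26/32 = 81% with 62.5% agreement among Fight Fatigue participants, 17.5 percentage points below the 80% mark. This assumes 20% attrition, equal by arm, and full agreement among controls. With less than full agreement among controls, the intervention arm must supply more. The probabilities in step 3 show that a divergence is plausible under the assumed rates; they do not forecast one.

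The mean-score flag needs its status stated. Its scale-based figures rest on the assumed five-point scale.

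**What to change.** - Apply the more-than-80%, agree-or-higher criterion to retained Fight Fatigue participants.
- Give a 95% interval for precision only, not as a test that must clear 80%. With 16 in the arm, even 16/16 has an exact lower limit of 0.025^(1/16) = 79.4%.
- Report control-arm ratings separately, and retention by arm next to the overall figure.
- State that the 80% proportion is the governing criterion. State that the mean-score flag is descriptive, computed per arm, and that not triggering it does not count as acceptable.

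The cost is a change of wording and a wider interval for the main acceptability estimate: about ±20 points at n = 16, against about ±14 for the pooled sample. No extra participants, visits or questionnaires are needed.
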